## Abstract

*Objective*. Sublingual microcirculatory alterations are associated with an adverse prognosis in several critical illness subgroups. Up to now, single-center studies have reported on sublingual microcirculatory alterations in ICU patient subgroups, but an extensive evaluation of the prevalence of these alterations is lacking. We present the study design of an international multicenter observational study to investigate the prevalence of microcirculatory alterations in critically ill: the Microcirculatory Shock Occurrence in Acutely ill Patients (microSOAP). *Methods*. 36 ICU's worldwide have participated in this study aiming for inclusion of over 500 evaluable patients. To enable communication and data collection, a website, an Open Clinica 3.0 database, and image uploading software have been designed. A one-session assessment of the sublingual microcirculation using Sidestream Dark Field imaging and data collection on patient characteristics has been performed in every ICU patient >18 years, regardless of underlying disease. Statistical analysis will provide insight in the prevalence and severity of sublingual alterations, its relation to systemic hemodynamic variables, disease, therapy, and outcome. *Conclusion*. This study will be the largest microcirculation study ever performed. It is expected that this study will also establish a basis for future studies related to the microcirculation in critically ill.

## 1. Introduction

The microcirculation plays a pivotal role in oxygen delivery to the tissue [1]. It is believed to be a key player in several disease states, such as sepsis and shock. The development of Orthogonal Polarizing Spectral (OPS) imaging and more recently Sidestream Dark Field (SDF) imaging has enabled bedside imaging of the—predominantly sublingual—microcirculation [2, 3]. Main advantage of SDF/OPS imaging is the ability to visualize true capillary hemodynamics in a noninvasive way at the bedside, thereby providing functional information related to the microcirculation where oxygen delivery to the parenchymal cells takes place. With SDF/OPS imaging, the presence of microcirculatory alterations in different critical care patient subgroups, such as sepsis, heart failure, and major surgery, has been widely explored during the past decade [4–9]. These microcirculatory alterations appear to be associated with an adverse prognosis; they are more severe in nonsurvivors in comparison to survivors in sepsis and heart failure, and are associated with the development of complications in abdominal surgery [4–12]. The aforementioned studies have all shown that microcirculatory alterations are apparent in the presence of more or less normal systemic haemodynamic parameters, thereby stressing the potential importance of the microcirculation as an additional target for resuscitation. Several interventions, ranging from vasoactive drugs and fluid therapy to circulatory assist devices, have been shown to have varying effects on their capacity to influence microcirculatory failure [7, 13–22]. 

Although a randomized controlled clinical trial (RCT) is considered as the highest level of evidence in medical research, the Empirics already realized the importance of observation for gaining a better understanding of diseases [23, 24]. Recent literature acknowledges the advantages of a solid observational study as a powerful tool to include large patient numbers with a variety of backgrounds, making the results easier to extrapolate to daily practice as opposed to RCTs with limited inclusion numbers due to stringent inclusion and exclusion criteria. This has especially been advocated for intensive care patients where several large RCTs fail to demonstrate beneficial effects of interventions. The heterogeneous nature of patients and applied therapy as well as uncertain underlying pathophysiology has been associated with this failure, emphasizing the need for more observational studies in intensive care patients to gain a better understanding of both patient characteristics and effects of interventions [25–29].

In microcirculatory research, the presence and significance of microcirculatory failure has been repeatedly demonstrated in single center studies with a limited number of patients in a variety of different ICU populations. However, a solid estimation of the prevalence of microcirculatory alterations in intensive care patients is not available as yet. Therefore, our aim was to conduct a multicenter observational study to map the prevalence of microcirculatory alterations in intensive care patients, irrespective of their underlying disease, to provide a solid basis for further (interventional) studies. The unique nature of this observational trial will be that it will not only observe the behavior of conventional clinical and hemodynamic variables but will also relate these to the behavior of a completely new unexplored physiological compartment in a multicentral international setting. In this paper we describe the trial design and methods we propose of evaluating the data.

## 2. Methods

Several large multicenter prevalence studies in critical care settings have been conducted, such as the Sepsis Occurrence in Acutely ill Patients (SOAP) study, the European Prevalence of Infection in Intensive Care (EPIC) study and the Columbian internet based Observatorio Nacional de Sepsis Pediátrica (ONASEP) [30–32]. We aimed for a similar study design.


ICU's were selected based on SDF/OPS availability, established skills in OPS/SDF imaging as demonstrated in a separate teaching course, and/or publications in this field. For image quality check, centers were asked to provide a representative SDF/OPS video of a septic patient and a healthy volunteer, enabling feedback on image quality. During an investigators meeting in March 2011, the study was scheduled for the second week of September 2011. For logistic reasons, it was decided that centers could choose two or more consecutive days for performing measurements. To prevent overlap of patient inclusion, ICU's were divided into (virtual) units and measured as one unit per day. A medical steering committee was formed to oversee the study, including representatives from the different continents as well as the major centers in the participating countries. The medical steering consisted of, [name], MD, PhD; [name], MD; [name]; [name], MD; [name], MD, PhD; [name], MD, PhD; [name], MD, MPH; [name], MD, PhD; [name], PhD. The study is coordinated from Medical Center Leeuwarden by the principal investigator ([name], MD, PhD), a dedicated physician in charge of running the communication ([name], MD) and a research nurse ([name]). The study center ensures communication with and between study centers, coordinates study logistics, and manages data analysis.

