### 2.2. Patient Selection

Every ICU patient ≥18 years, regardless of the underlying disease, was eligible for inclusion. Informed consent was obtained in accordance with local ethics approval. Participation in another study was no exclusion criterion, except when contradictory to local regulations. Patients <18 years or without informed consent were excluded, as well as patients with mucosal bleeding/injury or recent maxillofacial surgery that interfered with SDF/OPS imaging.

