### 2.5. Data Collection

The sublingual microcirculation was measured once in every patient. In line with internationally accepted consensus, 3 to 5 stable sublingual microcirculatory image sequences of 10–20 seconds were obtained for every patient [34, 35]. Along with the SDF/OPS imaging, data on demographics, reason for ICU admission, illness severity scores, haemodynamics, laboratory values, and treatment were collected. Afterwards, information on ICU/hospital length of stay and ICU/hospital mortality will be collected.

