#### 2.7.3. Statistical Analysis

Descriptive statistics will be used to describe the study population. Further statistical analysis will be conducted to relate the microcirculatory alterations to the severity of disease and other parameters. The primary outcome measure is the prevalence of microcirculatory alterations. There is no consensus about the thresholds for a “normal” and an “abnormal” microcirculation. Several researchers have reported on values of several microcirculatory variables in healthy volunteers; MFI of capillaries (<20 *μ*m) is reported to be 3.0 [2.9–3.0] (median [IQR]), 2.82 (0.1), and 2.97 (0.03) (mean(SD)) (IQR = interquartile range, SD = standard deviation) [5, 11, 42]. Therefore, one expects 95% of healthy subjects to have a small vessel MFI between 2.62 and 3 [11]. In healthy volunteers, PPVs (small vessels) well above 90% are described, whereas in septic patients, a capillary PPV of 78% (23%) is described [11, 42, 43]. In septic shock, norepinephrine dose >0.1 microgram/kg/min and a lactate >2 mmol/L were associated with a significantly lower PVD (12 [8–15] versus 14 [11–17] n/mm^2^ for norepinephrine dose >0.1 microgram/kg/min and 10 [8–13] versus 14 [11–17] n/mm^2^ for lactate >2 mmol/L), as well as a significantly lower PPV (80 [70–91] versus 100 [90–100]% for norepinephrine dose >0.1 microgram/kg/min and 82 [71–99] versus 93 [84–100]% for lactate >2 mmol/L) [44]. In uncomplicated major abdominal surgery, preoperative PPV (small vessels) was 89% (83–95) versus 79% (73–92) in patients who developed complications postoperatively [4]. In this study, ROC curves will be used to find cut off values of microcirculatory variables in relation to morbidity and mortality.

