## 3. Discussion

This study will be by far the largest cohort of in vivo microcirculation research. We aim to provide insight in the worldwide prevalence and distribution of microcirculatory alterations. The questions we hope to answer are the following:

Does the presence of microcirculatory alterations indicate impending bad outcome in terms of morbidity and mortality?Does the presence of microcirculatory alterations provide a more sensitive indicator of morbidity and mortality then conventional hemodynamic and oxygen derived parameters? Is the presence of microcirculatory alterations related to applied therapy, such as fluid therapy and vasopressors?Is there a difference between microcirculatory alterations in different patient (sub-) groups, and how are these geographically distributed, as well as over time?

We expect that the results of our study will make clinicians more aware of the presence and importance of microcirculatory alterations in daily practice, thereby leading to better identification of patients who are at risk of an unfavorable outcome. Furthermore, we hope to trigger researchers to develop methods enabling easier bedside evaluation of the microcirculation for detection of those at risk of “microcirculatory failure”, as well as interventions aimed at ameliorating the microcirculation. Hopefully, by putting the microcirculation in a central position in future ICU practice, outcome of critically ill patients will be improved.

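### ROC cut-offs and mortality associations pool patients imaged on any ICU day from a length-biased one-day census; they should also be reported by ICU day at imaging

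*Protocol article*

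**What the plan says.** The design is fixed in three places of the protocol article. The Methods paragraph on centre selection and study days (just before section 2.2) says that "centers could choose two or more consecutive days for performing measurements" and, to avoid including a patient twice, that "ICU's were divided into (virtual) units and measured as one unit per day". Section 2.2 says: "Every ICU patient ≥18 years, regardless of the underlying disease, was eligible for inclusion". It sets no limit on time since ICU admission. Section 2.5 says: "The sublingual microcirculation was measured once in every patient". No ICU day is fixed for that measurement.

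The opening of section 2 names several multicentre prevalence studies and adds "We aimed for a similar study design". Section 2.7.3 follows this: "The primary outcome measure is the prevalence of microcirculatory alterations".

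The same section then uses the sample for prognosis: "ROC curves will be used to find cut off values of microcirculatory variables in relation to morbidity and mortality". It also plans correlations with mortality and forward stepwise logistic regression. The first question in the Discussion is: "Does the presence of microcirculatory alterations indicate impending bad outcome in terms of morbidity and mortality". Length of stay and mortality in ICU and hospital are collected after imaging (section 2.5). The article mentions no analysis by ICU day at imaging. The last Discussion question touches on change over time but does not tie it to time since admission, and one measurement per patient could not answer it within patients.

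**The concern.** A patient enters a one-day census only if still in the ICU that day, so the chance of inclusion grows with length of stay. A patient who stays 10 days is 10/2 = 5 times as likely to be caught as one who stays 2 days. Patients who die or leave early are under-sampled.

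A prevalence estimate can live with this, because it describes the patients present. A prognostic estimate is harder to interpret. The pooled odds ratio and ROC curve mix patients imaged within hours of admission with patients imaged after weeks, who have already survived the early risk and whose alterations may have resolved or appeared since. Such a cut-off has no defined time origin.

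At stake are the answer to the first Discussion question and any threshold carried into the goal-directed trial foreseen in the Conclusion. Section 2.7.3 concedes that no threshold is agreed and turns to ROC curves for cut-offs. If those cut-offs also defined an alteration for the primary outcome, which the article does not say, the pooling would reach that outcome too.

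**Working it through.** **Inputs.** From the article: one unit per day, one measurement per patient, no limit on time since admission, about 500 patients (section 4). That size matches ten times the upper end of the 25 to 50 patients in earlier studies (section 2.7.1): 10 × 50 = 500. The article gives no stay distribution, mortality or persistence of alterations, so it has no figure to reproduce on this point. Assumed here: lognormal ICU stay L with median m of 2 to 4 days and log-SD s of 0.5 to 1.2; mortality 20%; alteration at admission in 50% of non-survivors and 20% of survivors. Admission odds ratio: (0.5/0.5)/(0.2/0.8) = 4.0. Admission prevalence: 0.2 × 0.5 + 0.8 × 0.2 = 26%.

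**Step 1: over-representation of long stays.** With inclusion proportional to L, the share with total stay above 7 days is 1 − Φ(ln(7/m)/s) among admissions and 1 − Φ((ln(7/m) − s²)/s) in the census.

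| m, s | Admissions | Census |
|---|---|---|
| 2, 0.5 | 0.6% | 2% |
| 3, 0.5 | 4.5% | 12% |
| 2, 1.0 | 10.5% | 40% |
| 3, 1.0 | 20% | 56% |
| 4, 1.2 | 32% | 77% |

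Across the assumed range the share rises about two- to fourfold. Whether long stays form a majority depends on the skewness of stays.

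**Step 2: mortality odds ratio, alterations persisting.** If alteration status does not change during the stay, each cell of the 2 × 2 table is weighted by its mean stay. At equal log-SD, this gives: census OR = 4.0 × (altered/unaltered median stay in non-survivors) ÷ (the same ratio in survivors).

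- Equal stays: 4.0 × 1 ÷ 1 = 4.0, no bias.
- Altered non-survivors die early (median 1.5 v 4 days): 4.0 × 1.5/4 = 1.5.
- The same, and altered survivors stay longer (5 v 3): 1.5 ÷ (5/3) = 0.9.
- Altered non-survivors die late (5 v 3): 4.0 × 5/3 = 6.7.

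**Step 3: alterations resolving.** Imaging falls at a uniform point in the stay. With resolution rate r per day, the altered fraction is multiplied by g = E[(1 − exp(−rL))/r]/E[L]. With m = 3 and s = 1.0:

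- r = 0.1 in both groups: g = 0.644, altered 32.2% v 12.9%, OR 3.2.
- r = 0.3 in both: g = 0.398, altered 19.9% v 8.0%, OR 2.9.
- r = 0.02 in non-survivors, 0.1 in survivors: g = 0.889 and 0.644, OR 5.4.
- r = 0.05 in non-survivors, 0.3 in survivors: g = 0.773 and 0.398, OR 7.3 (7.4 by simulation).

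Across steps 2 and 3, the 26% admission prevalence appears in the census as 10% to 31%.

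**Step 4: why stratify by ICU day.** The joint density of stay L and elapsed time t in the census is proportional to f(L) for t < L. Given t, this is f(L | L > t): all admissions still present at t, with no further length bias. Each ICU-day stratum is therefore close to a landmark population with a defined time origin. In one assumed simulation (early excess hazard, 15% of alterations resolving per day), the odds ratio was 5.3 at admission and 2.8 pooled. By day of imaging it was 5.1 (day 0), 3.3 (days 1 to 3), 1.9 (days 4 to 7) and 1.8 (later). Day as a main effect only moved the pooled value to 2.9, so the stratum-by-alteration term is needed.

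**The case against.** The strongest reply is that this is a prevalence study, modelled on prevalence studies, and that a one-day census estimates point prevalence correctly. That stands. A reader might infer that the primary outcome is biased because it differs from the share of admissions with alterations. The article never claims prevalence per admission; its wording merely leaves the population open.

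Two further inferences are tempting and also fail. One is that long-stay patients dominate the sample: over-representation follows from the design, but a majority does not (12% to 56% for the middle rows of the step 1 table). The other is that the prognostic signal is diluted: steps 2 and 3 show weakening, strengthening, near-reversal and no change, depending on inputs that the article does not give.

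It can also be said that the article condenses a full protocol, that its regression candidates are not listed, and that ICU day may be handled elsewhere. This stands as a caution: absence from the article does not show absence from the full plan. It does not remove the point, because the article itself states the cut-offs and associations without reference to ICU day and gives them a prognostic reading.

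Finally, impending outcome can be asked of any patient present, early or late. That is fair, so the early stratum need not take precedence.

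**Conclusion.** The point holds for the prognostic analyses and is worth a change. The design alone establishes that inclusion depends on length of stay and that the ICU day of imaging is arbitrary. The size and direction of the effect on the mortality odds ratio are not established. An admission value of 4.0 can appear as about 0.9 to 7.3, all on assumed stays, mortality and resolution rates. Because the direction is unknown, a reader of the pooled result cannot correct for it. For the primary outcome only the label needs attention.

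**What to change.** In section 2.7.3:

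1. Label the primary estimate as point prevalence among patients in the ICU on the study day.
2. Derive ICU days before imaging from the imaging date and the ICU admission date. The article does not name the admission date as a data item, but length of stay presupposes it.
3. Report prevalence, the mortality odds ratio and the ROC results by prespecified strata of that variable (for example 0–1, 2–7 and >7 days), with a stratum-by-alteration term, beside the pooled result.
4. Describe pooled prognostic results as conditional on being in the ICU that day.

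The cost is one derived variable and some wording, with no new patients or procedures. The downside is precision. If about 28% of patients were imaged on days 0–1 (a simulated figure), that stratum holds 0.28 × 500 = 140 patients and, at an assumed 20% mortality, 28 deaths. Its intervals are about √(500/140) = 1.9 times as wide as the pooled ones. The stratified ROC results should therefore be called exploratory.

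Weighting by the inverse of length of stay is not a substitute. It recovers the average state over a stay, not the state at admission: with m = 3, s = 1.2, 30% altered at admission and 15% resolving per day, it gives about 22%. It also cuts the effective sample to exp(−s²) = exp(−1.44) = 24%, roughly 120 of 500.

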### 2.2. Patient Selection

Every ICU patient ≥18 years, regardless of the underlying disease, was eligible for inclusion. Informed consent was obtained in accordance with local ethics approval. Participation in another study was no exclusion criterion, except when contradictory to local regulations. Patients <18 years or without informed consent were excluded, as well as patients with mucosal bleeding/injury or recent maxillofacial surgery that interfered with SDF/OPS imaging.

### 2.3. Ethics Approval

A study protocol was provided to participating centers. Every participating center obtained ethics approval according to local legislation. A copy of the ethics approval was sent to the study coordinator before start of the study. Written informed consent was obtained of all included subjects, unless the local ethics committee specifically allowed a waiver in this respect.

The study was registered at http://www.clinicaltrials.gov/ (NCT01179243). No (industry) sponsorship has been received for this investigator-initiated study, with the exception of a local hospital fund.

### 2.4. SDF/OPS Imaging

Sublingual OPS and SDF imagings are used for microcirculatory imaging at the bedside with the potential of quantification both at the bedside and offline [33–35]. In short, the OPS and SDF analogue cameras are incorporated in handheld devices, emitting polarized, respectively, stroboscopic green light, with a wavelength within the absorption spectrum of haemoglobin, thereby depicting erythrocytes as black cells. The area of visualization is approximately 1 mm^2^. These techniques are described in detail elsewhere [2, 3]. Offline computer assisted analysis yields information on both convection and diffusion. Microvascular flow index (MFI) is calculated to describe convection in a semiquantitative way; the predominant flow in all quadrants of the SDF/OPS image is scored for different vessel sizes, using a scale ranging from 0 (no flow) to 3 (continuous flow). The averaged flow score yields the MFI for each image. MFI has been shown to correlate well with red blood cell velocity [36]. To obtain information on diffusion, several measures of functional capillary density are calculated, using a grid dividing the image into 16 segments. Every vessel crossing the grid is counted; furthermore, for each vessel crossing the grid, the type of flow using the MFI scale is used, a flow of 0 (no flow) or 1 (intermittent flow) is considered as nonperfused, whereas a flow of 2 (sluggish) or 3 (continuous) describes perfused vessels. By using these data, several measures of functional capillary density can be calculated, including proportion of perfused vessels (PPVs) and perfused vessel density (PVD). Dividing the numbers of perfused grid crossings by the total number of grid crossings yields the PPV; the PVD is calculated as the number of perfused grid crossings divided by the total grid length. In the same way, total vessel density (TVD) can be calculated. A detailed description of MFI and measures of functional capillary density can be found elsewhere [34, 35].

### 2.5. Data Collection

The sublingual microcirculation was measured once in every patient. In line with internationally accepted consensus, 3 to 5 stable sublingual microcirculatory image sequences of 10–20 seconds were obtained for every patient [34, 35]. Along with the SDF/OPS imaging, data on demographics, reason for ICU admission, illness severity scores, haemodynamics, laboratory values, and treatment were collected. Afterwards, information on ICU/hospital length of stay and ICU/hospital mortality will be collected.

